#### 2.4.6. Withdrawal Criteria

Participants who privately cease to accept medical treatment or conduct testing or who become impossible to contact are also considered withdrawnParticipants who cannot continue because of poor clinical efficacy, intolerance due to adverse reactions, economic reasons, or moves

### 2.5. Interventions

The participants will be divided into either the intervention group or the control group (1 : 1). The control groups will conduct lifestyle intervention alone, and the intervention group will use TCPMs on the basis of lifestyle intervention.

#### 2.5.1. Lifestyle Intervention

The guidelines for the prevention and treatment of type 2 diabetes (2017 edition) suggest that subjects with abnormal glucose metabolism should reduce their risk of T2DM through controlling diet and strengthening exercise. Lifestyle intervention will be implemented by medical staff, and a health management application will be used. Firstly, healthy lifestyle education will be developed every 2 weeks. The aim of the education is to promote changes in lifestyle behaviors strongly associated to overweight/obesity and the risk of T2DM and to provide personalized health behavior guidance for different target groups. Secondly, the trial will advocate a healthy reasonable match of calories, carbohydrates and protein, and low-salt low-fat and low-sugar diet. The staple food is suggested to be quantitative with the combination of coarse food grain and wheat flour and rice, the daily consumption of vegetables should be enhanced, regular intake of fish and poultry is suggested, appropriate intake of eggs and livestock meat and limited intake of processed meats is suggested, and the intake of sugar, sugar-sweetened beverages, and energy-dense foods is suggested to be reduced. Thirdly, physical activity of moderate intensity, such as brisk walking, swimming, tai chi, and eight-section brocade, is engaged for at least 150 minutes per week. Through the lifestyle interventions mentioned above, the goal for overweight/obese participants is 5–10% of weight reduction in 6–8 months.

#### 2.5.2. Syndrome Differentiation of Traditional Chinese Patent Medicine

The intervention group will use TCPMs based on syndrome differentiation. If the syndrome belongs to dampness-heat accumulation in the spleen, it should be treated with JinQi-Jiangtang tablet (3 tablets, three times per day). If the syndrome belongs to spleen deficiency and phlegm obstruction, it should be treated with Shenzhu Tiaopi granule (2 bags, three times per day). If the syndrome belongs to liver depression and qi stagnation, it should be treated with Yue Ju pills (1 bag, three times per day). If the syndrome belongs to qi-yin dual insufficiency, it should be treated with Qizhi jiangtang capsule (2.5 g three times per day).

#### 2.5.3. Concomitant Treatment

All the participants will receive the standard intervention of blood pressure, paying close attention to other cardiovascular risk factors and giving appropriate intervention measures. Moreover, the participants will not change the drugs used to treat chronic diseases.

### 2.6. Outcome Measurement

#### 2.6.1. Indexes of End Point

Incident diabetes according to the guideline for the prevention and treatment of type 2 diabetes (2017 edition)Normalization of Blood Glucose, FPG <5.6 mmol/L or 2h PBG <7.8 mmol/L

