## 1. Background

Type 2 diabetes mellitus (T2DM) and its precursor prediabetes are growing public health concerns. In China, it is estimated that one-third of the adult population have prediabetes, and experts have projected that more than 470 million people will have prediabetes by 2030 [1, 2]. Prediabetes is characterized by both mild impaired fasting blood glucose (IFG) and/or impaired glucose tolerance (IGT). People with IGT show normal fasting plasma glucose values (FBG less than 7.0 mmol/L) and abnormal two-hour postprandial blood glucose values (2h PG 7.8 to 11.0 mmol/L). People with IFG only demonstrate an abnormal FBG values (FBG 6.1 to 6.9 mmol/L; 2h PG less than 7.8 mmol/L, if measured). Prediabetes perpetuates pancreatic *β*-cell dysfunction and nearly always precedes T2DM. Furthermore, prediabetes and T2DM often accompany overweight/obesity and dyslipidemia, which are responsible for increased risk of all-cause mortality, cardiovascular disease, and stroke [3]. Therefore, the prevention of T2DM in prediabetic patients is a topic of importance. Guidelines for the prevention and control of T2DM in China recommend that lifestyle interventions and weight loss can prevent prediabetes progress to T2DM [4]. However, prediabetic individuals feel difficult to change their lifestyle, and the challenges also posed in successful implementation and maintenance of certain lifestyle modifications. The pharmacological options recommended in the guidelines for prediabetes are limited.

Currently, there are more than 100 TCPMs used for preventing and treating T2DM, and several systematic reviews have demonstrated that TCPMs combined with moderate lifestyle modification may reduce the risk of progression to T2DM and increase the possibility of regression toward normoglycemia [5, 6]. TCPMs contain various active ingredients, which possess different efficacies and therapeutic principles. In the process of TCM clinical practice, a comprehensive analysis of symptoms and signs is conducted which has implications for determining the cause, nature, and location of the illness and the patient's physical condition and eventually deciding which kinds of TCPMs they should use. Here, our research team will implement a multicenter, prospective cohort study to investigate the efficacy and safety of TCPMs in the prevention of T2DM on the basis of syndrome differentiation and treatment. This work describes the methodology and specific details underlying the study.

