## 2. Methods

### 2.1. Trial Design

This study is a multicenter cohort study with two arms. A total of 600 participants will be recruited. The participants will be divided into either intervention or control groups according to their own desire, and the exposure factor is the application of TCPMs. All participants will be encouraged to lead a healthy lifestyle, and the intervention group also used TCPMs based on syndrome differentiation. Incident diabetes and normalization of blood glucose are indexes of end point. Safety assessments and adverse event monitoring will also be conducted. The treatment duration is set for 24 weeks, and we will follow-up for another 2 years.

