### 2.4. Eligibility Criteria

#### 2.4.1. Diagnostic Criteria

Impaired glucose tolerance (IGT) is defined according to the 1999 WHO criteria: FBG <7.0 mmol/L or 2h PBG ≥7.8 and <11.1 mmol/L.

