### 2.10. Sample Size Calculation

According to previously published research [11], the annual conversion rate of IGT into T2DM was 1.5% in the TCM group and 10% in the control group. We predicted that the annual conversion rate of IGT into T2DM was 5.7% in the TCM comprehensive intervention group. Therefore, assuming that *α* = 0.05 and *β* = 0.1 according to the one-sided test, u*α* = 1.645 and u*β* = 1.282, and the data will be placed in the formula to obtain *n* = 299.94. Therefore, each group needs more than 300 participants, for a total of 600 participants.

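### The normalization end point is met by either a fasting or a 2-hour value alone, so some eligible participants can meet it at week 0 and others while still abnormal

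*Protocol article*

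**What the plan says.** Section 2.1 states that "Incident diabetes and normalization of blood glucose are indexes of end point". Section 2.6.1 defines the second of these as "Normalization of Blood Glucose, FPG <5.6 mmol/L or 2h PBG <7.8 mmol/L" and the first as "Incident diabetes according to the guideline for the prevention and treatment of type 2 diabetes (2017 edition"), without printing the guideline's cut-offs. The normalization rule asks for no change from baseline and no absence of diabetes.

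Two places describe the entry condition. The Background says "People with IGT show normal fasting plasma glucose values (FBG less than 7.0 mmol/L) and abnormal two-hour postprandial blood glucose values", the latter being 7.8 to 11.0 mmol/L. Section 2.4.1 prints the operative criterion as "FBG <7.0 mmol/L or 2h PBG ≥7.8 and <11.1 mmol/L". Section 2.4.3 requires IGT still to be present after a month of diet and exercise. None of these sets a lower limit on fasting glucose.

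The Background also describes isolated IFG: "People with IFG only demonstrate an abnormal FBG values", given as 6.1 to 6.9 mmol/L with a 2-hour value below 7.8 if measured.

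**The concern.** In IGT it is the 2-hour value that is abnormal. The fasting value may be anywhere below 7.0. A rule satisfied by a fasting value below 5.6 alone can therefore be met without any change in the abnormality that brought the participant into the study. The other half of the rule has the mirror problem: a 2-hour value below 7.8 counts whatever the fasting value is.

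Two consequences matter for the analysis. Participants who meet the rule at entry and go on meeting it add the same block of responders to both groups, which dilutes a real difference. Also, participants choose their own group (Section 2.1), and Section 2.11 names unadjusted between-group tests. If the groups differ at baseline in the share with FPG below 5.6, that difference passes directly into the normalization rates and looks like a treatment effect.

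**Working it through.** **Step 1. Apply the printed rules to example values (mmol/L).**

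| FPG | 2h PBG | Status from the article's own limits | Normalised with *or* | Normalised with *and* |
|---|---|---|---|---|
| 5.3 | 9.5 | IGT, eligible | Yes | No |
| 6.8 | 7.5 | IFG (Background) | Yes | No |
| 5.3 | 12 | Above the 11.1 ceiling of Section 2.4.1 | Yes | No |
| 7.2 | 7.0 | Above the 7.0 fasting ceiling | Yes | No |
| 5.2 | 7.0 | Both values below the normalization limits | Yes | Yes |

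The first two rows need nothing from outside the article. Calling rows three and four diabetic is an inference from the ceilings at which IGT ends (7.0 and 11.1), because the guideline's values are not printed.

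**Step 2. Could anything else in the article correct this?** Section 2.6.2 lists glucose changes as the primary outcome and does not redefine normalization. Section 2.11 does not restrict who is counted. Nothing makes the two end points mutually exclusive.

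**Step 3. Share already normalised at entry.** For participants who are IGT as the Background describes it, this equals the proportion with FPG below 5.6. The article gives no FPG distribution. Assume FPG is normal with mean m and SD s, truncated below 7.0:

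share = Φ((5.6 − m)/s) / Φ((7.0 − m)/s)

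- m = 6.2, s = 0.5: Φ(−1.2)/Φ(1.6) = 0.122, or 73 of 600.
- m = 5.4, s = 0.5: Φ(0.4)/Φ(3.2) = 0.656, or 394 of 600.

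Over m from 5.4 to 6.2 and s from 0.5 to 0.7 the range is about 12% to 66%. The width of that range shows that the share cannot be fixed from the article.

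**Step 4. Dilution, for illustration.** The article gives no expected normalization rates, so 30% and 42% are assumed. Let f be the share with FPG below 5.6 at entry, assume they stay there, and let everyone else normalise at the true rate:

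observed rate = f + (1 − f) × true rate

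Power is for two proportions, 300 per group, two-sided 0.05:

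power = Φ((d − 1.96 × SE0)/SE1)

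Here d is the observed difference, SE0 the pooled and SE1 the unpooled standard error.

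| f | Observed rates | Power |
|---|---|---|
| 0 | 30% vs 42% | 87% |
| 12% | 38% vs 49% | 74% |
| 30% | 51% vs 59% | 54% |
| 40% | 58% vs 65% | 44% |

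For f = 30%: 0.30 + 0.70 × 0.30 = 0.510 and 0.30 + 0.70 × 0.42 = 0.594, so d = 0.084, SE0 = 0.0406 and SE1 = 0.0405. Power = Φ(0.109) = 0.543.

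**Step 5. False effect from self-selection, for illustration.** Suppose there is no treatment effect, the true rate is 30% in both groups, and f is 45% in one group and 35% in the other. The observed rates are 0.45 + 0.55 × 0.30 = 61.5% and 0.35 + 0.65 × 0.30 = 54.5%. The 7-point gap is spurious, and a two-sided test at 0.05 would call it significant about 41% of the time.

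**The plan's own figure.** Section 2.10 gives 299.94 per group for conversion to diabetes, from yearly rates of 10% for controls and a predicted 5.7% under intervention. For 10% against 5.7% at the stated one-sided 0.05 and 90% power, (1.645 + 1.282)² × (0.10 × 0.90 + 0.057 × 0.943)/0.043² = 666, so 299.94 does not reproduce from the annual rates. That is a separate matter. Only the planned group size of 300 is borrowed here.

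**The case against.** **The *or* may be a drafting slip.** Section 2.4.1 has a similar *or* where the Background clearly means *and*, so the article may use the word loosely. That is plausible, and it makes this more likely a wording error than a chosen end point. It does not rescue the rule, because an analyst would code what is printed. Reading Section 2.4.1 literally makes matters worse: it would admit people with FPG below 7.0 and 2h PBG below 7.8, who also meet the end point at entry.

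**The illustration does not model the rule fully.** This stands. The true rates and baseline shares are assumed. Fasting values are taken to stay below 5.6, no one is lost, and participants who are not normalised at entry are given the true rate although the printed rule lets them qualify on either value. The figures show direction and plausible size, not a forecast.

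**The end point is not the main one.** This also stands. Section 2.6.2 makes changes in FBG, 2h PBG and HbA1c the primary outcome, and Section 2.10 sizes the study on conversion to diabetes. The study's stated power is not affected.

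**The 5.6 limit against 6.1.** A reader might infer that a fasting limit of 5.6 contradicts the Background's IFG threshold of 6.1. It does not. A normalization target may be stricter than the lower limit of a disease range.

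**Conclusion.** The rule is wrong as written. The week-0 and IFG examples follow from the article's own limits, with no assumption. The overlap with diabetes rests on the reasonable inference that diabetes begins where IGT ends. Coded as printed, one of the two end-point indexes cannot be read as a return to normal glucose.

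A reader might go further and infer that many or most participants would be normalised at entry. The article does not support that: it gives no fasting distribution, and the assumed range of 12% to 66% is too wide for more than saying that some can be. The fall in power from 87% to 54% and the 7-point false difference hold only under the assumptions stated with them.

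**What to change.** In Section 2.6.1 change *or* to *and*. Normalization then requires FPG <5.6 mmol/L and 2h PBG <7.8 mmol/L at the same visit, in a participant who has not met the incident-diabetes end point by that visit. The 5.6 limit can stay. Section 2.4.1 should be reconciled with the Background's description of IGT. Once entry requires a 2-hour value of at least 7.8, no participant can be normalised at week 0 under the revised rule.

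The cost is a short amendment before analysis. Table 1 already schedules both glucose tests at every visit from week 0, so no new data are needed, and the sample size does not change. The downside is a lower reported normalization rate.

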#### 2.6.2. Primary Outcome

The primary outcome is the changes of fasting plasma glucose (FBG), two-hour postprandial blood glucose (2h PBG), and glycosylated hemoglobin (HbA1c). Blood glucose is evaluated every 4 weeks, and HbA1c is evaluated every 12 weeks.

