### 2.11. Statistical Analysis

Three datasets will be used for statistical analysis, including a full-analysis set (FAS), per-protocol analysis set (PPS), and safety analysis set (SS). The FAS is the dataset composed of participants who have at least one postmedication evaluation data. The last observation carried forward (LOCF) method will be used for the missing data supplement. The PPS is the dataset composed of participants who meet the inclusion criteria, show good compliance, and complete the treatment plan. The SS is the dataset of all participants randomized to study, and safety record will be assessed, including adverse events and laboratory test results. All statistical tests are two-sided tests, and *P* < 0.05 will be considered statistically significant. Enumeration data will be expressed as frequency and analyzed using the chi-square test or Wilcoxon rank sum test. Measurement data will be described by means, standard deviation, maximum value, and minimum value and compared between groups using the group *t*-test, Fisher's exact test, or Wilcoxon rank sum test. Statistical analysis will be completed by the third-party statisticians.

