## 3. Discussion

In the present clinical practice in China, prevention of T2DM mainly depends on the improvements in unhealthy lifestyles, which is hard to persist in. Several large-scale trials have demonstrated that use of some hypoglycemic drugs can decrease the incidence of diabetes to various degrees in those with prediabetes [12–15], though none are approved by the U.S. Food and Drug Administration, specifically for diabetes prevention. The cost, adverse reactions, tolerance, and other factors are also needed to be considered [4, 16]. TCM may hold a promise in the prevention of T2DM because of its characteristics of “treat disease before it arises,” which include strengthening the body constitution and regulating the high-risk factors leading to diabetes; in addition, TCM could also control the development of T2DM. This cognition corresponds with the thought of the prevention of T2DM. Prediabetes may fall under the TCM patterns of “spleen pyretic abundance,” etc. [17]. The main pathogenesis lies in spleen and stomach congestion, dampness-heat accumulation in the spleen, spleen deficiency and phlegm obstruction, liver depression and qi stagnation, and qi-yin dual insufficiency [9, 10]. In China, many prediabetic patients are more likely to choose the complementary TCPMs. Postmarketing TCPMs possess steady drug composition and defined dosage, which is convenient to observe the efficacy. In recent years, some randomized controlled trials (RCTs) have proved that TCPMs alone or TCPMs combined with lifestyle modification could be an effective intervention for the preventative treatment of T2DM [18–20]. Now, we aim to implement a clinical trial to observe the efficacy of TCPMs in the prevention of T2DM in Chinese subjects. The strength of our trial is that the trial design is a prospective cohort study, not an RCT, and the choice of intervention drugs in our trials is based on syndrome differentiation and treatment, which are more in accord with the clinical practice of TCM. The treatment duration is 6 months, and follow-up is continued for another two years, which is to observe the short-term and long-term effects of TCPMs. As to outcome assessment, we emphasize for incident diabetes and normalization of blood glucose, improvement of symptoms is also important for prediabetic patients to increase the quality of life.

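### The sample size and its 90% power concern conversion to diabetes, but the declared primary outcome is three glucose changes that no power calculation covers, and the two sets of outcomes are not ranked

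*Protocol article*

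**What the plan says.** All references are to the protocol article.

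- **Primary outcome (section 2.6.2).** "The primary outcome is the changes of fasting plasma glucose (FBG), two-hour postprandial blood glucose (2h PBG), and glycosylated hemoglobin (HbA1c"). The timing given is a measurement frequency: "Blood glucose is evaluated every 4 weeks, and HbA1c is evaluated every 12 weeks". Table 1 schedules each glucose measure at ten post-baseline visits and HbA1c at six. None is named as decisive.
- **End-point tier (sections 2.1 and 2.6.1).** "Incident diabetes and normalization of blood glucose are indexes of end point". This tier is listed before the primary outcome and apart from the secondary outcomes of section 2.6.3. Its rank is not given.
- **Sample size (section 2.10).** The cited research is reported thus: "the annual conversion rate of IGT into T2DM was 1.5% in the TCM group and 10% in the control group". Then: "We predicted that the annual conversion rate of IGT into T2DM was 5.7% in the TCM comprehensive intervention group". The calculation proceeds "assuming that *α* = 0.05 and *β* = 0.1 according to the one-sided test" and arrives at 299.94 per group, 600 in total.
- **Analysis (section 2.11).** "All statistical tests are two-sided tests, and *P* < 0.05 will be considered statistically significant".
- **Discussion (section 3).** On outcome assessment: "we emphasize for incident diabetes and normalization of blood glucose".

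**The concern.** The aim (preventing type 2 diabetes), the sizing and the Discussion all point to incident diabetes, while section 2.6.2 gives the title of primary outcome to three continuous measurements. Sections 2.6.2 and 2.10 are both printed in full and do not fit together. An analysis plan may add detail, but it cannot make a calculation on conversion rates justify the sample size for changes in FBG, 2h PBG and HbA1c.

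At stake is what the study can conclude. A reader cannot tell which result decides it, and the 90% power could be credited to an outcome for which it was never calculated. A significant fall in one glucose measure could be presented as the primary result of a diabetes-prevention study while the outcome used for sizing is inconclusive.

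**Working it through.** **1. The plan's own figure.** Inputs from section 2.10: p1 = 0.10, p2 = 0.057, u-values 1.645 and 1.282.

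n per group = [u_α·√(2p̄(1−p̄)) + u_β·√(p1(1−p1)+p2(1−p2))]² / (p1−p2)²

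- p̄ = 0.0785, so 2p̄(1−p̄) = 0.14468, with root 0.38036.
- p1(1−p1)+p2(1−p2) = 0.09 + 0.05375 = 0.14375, with root 0.37915.
- n = (1.645×0.38036 + 1.282×0.37915)² / 0.043² = 1.2360 / 0.001849 = 668.5, so **669 per group**. With 1.96 in place of 1.645 it is 821.

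The stated 299.94 does not follow from the annual rates. It is approached (301 to 307, depending on the formula) if both rates are doubled to 20% and 11.4%, as for two years. The protocol does not state that step. On those doubled rates the two-sided requirement would be about 374 per group, with 83% power at 300.

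**2. Power for incident diabetes at 300 per group, stated annual rates.**

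Power = Φ{[(p1−p2)·√300 − u_α×0.38036] / 0.37915}, with 0.043×17.3205 = 0.74478.

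- Two-sided: (0.74478 − 1.96×0.38036)/0.37915 ≈ −0.002, so **50%**.
- One-sided: (0.74478 − 1.645×0.38036)/0.37915 = 0.314, so **62%**.

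A longer horizon helps. Compounding the rates to 2.5 years, close to the 30-month visit in Table 1, gives 1−0.9^2.5 = 23.2% and 1−0.943^2.5 = 13.6%, with two-sided power of 85%. This assumes that both annual rates stay constant after treatment ends at week 24 and that nobody is lost.

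**3. Detectable difference for one continuous change at 300 per group, two-sided.** The documents give no SD and no expected difference, so the result is in SD units: δ = (z_{1−α/2} + z_power)·√(2/300), with √(2/300) = 0.08165.

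- α = 0.05, 80% power: (1.960 + 0.842)×0.08165 = **0.23 SD**; at 90% power, 0.26 SD.
- α = 0.05/3 = 0.0167, 80% power: (2.394 + 0.842)×0.08165 = **0.26 SD**; at 90% power, 0.30 SD.

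Power over an assumed range of true differences:

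| True difference | α = 0.05 | α = 0.0167 |
|---|---|---|
| 0.1 SD | 23% | 12% |
| 0.2 SD | 69% | 52% |
| 0.25 SD | 86% | 75% |
| 0.3 SD | 96% | 90% |

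**4. Error rate for three tests at two-sided 0.05, one visit.** If independent, 1 − 0.95³ = 14.3%. For correlated tests, equicorrelated normal statistics were simulated (1,000,000 draws). The correlations are assumptions. Both columns are for no true effect on any of the three.

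| Correlation | At least one significant | All three significant |
|---|---|---|
| 0 | 14.3% | <0.01% |
| 0.5 | 12.5% | 0.3% |
| 0.7 | 10.9% | 0.9% |
| 0.9 | 8.4% | 2.2% |

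Under an all-three rule the error cannot exceed 5%, because the rule requires every individual 5% test to reject.

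**The case against.** The strongest defence is that this is a condensed article. The success rule, the decisive visit and any multiplicity adjustment are commonly fixed in an analysis plan that is not shown, and the P < 0.05 sentence may be only a general threshold. That stands in part: the absence of those details does not by itself show an error. It does not answer the mismatch between sections 2.6.2 and 2.10 or the unranked end-point tier.

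Four stronger readings are tempting and are not supported:

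- **That the primary outcome is underpowered.** Step 3 does not show this. With 300 per group a difference of 0.23 SD is detectable at 80% power. What is missing is a justification.
- **That the error rate exceeds 5%.** This is so only if any one significant change counts as success, and no section says so.
- **That any visit could be chosen, with a far higher error rate.** No section describes a free choice of visit.
- **That incident diabetes was demoted to secondary.** Section 2.6.3 does not list it. It sits first, in its own tier, without a rank.

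**Conclusion.** The point holds in this form: the stated sample size and 90% power do not belong to the declared primary outcome, and the protocol does not reconcile its primary outcome with its end-point tier. This rests on the text alone.

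The multiplicity part is conditional: about 8% to 14% under an any-one rule (correlation 0.9 to 0), at most 5% under an all-three rule, with neither stated.

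Moving the label to incident diabetes does not restore 90% power. At the stated annual rates and 300 per group it is about 50% two-sided. The power figures assume two equal groups, unadjusted comparisons and no loss to follow-up. Those for glucose also depend on an SD that the documents do not give.

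The matter needs settling before analysis, because it decides what the study may claim.

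**What to change.** Choose one of the following before analysis, in the protocol and the registry record.

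- **Preferred:** name incident diabetes as the single primary outcome, in line with the aim and the sizing outcome, and state its time horizon. Make the week-24 changes in 2h PBG, FBG and HbA1c key secondary outcomes, in a fixed order or with Holm's procedure. State where normalization of glucose ranks.
- **Alternative:** keep the three changes as primary, fix week 24 as the decisive visit, and either apply Holm or state that all three must be significant. Rank the two end-point indexes below them.

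In either case restate the power at 300 per group under the two-sided test of section 2.11. For incident diabetes, report about 50% at the stated annual rates, or a recalculated figure for the stated longer horizon with its assumptions on rates and losses. For a glucose change, report the detectable difference (0.23 SD at 80% power, 0.26 SD at alpha 0.0167) and set it against an expected difference and SD. An all-three rule needs its own, lower, joint power.

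The cost is wording and a recalculation; no extra data are needed. The downside is that fewer outcomes carry a confirmatory claim and the stated power will look less favourable than 90%.

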### 2.7. Study Visits and Data Collection

The study is divided into two periods, a 24-week drug intervention period and a 24-month follow-up period. After the intervention period commences, telephone visits will take place every 2 weeks and outpatient visits every 4 weeks. When the follow-up period commences, outpatient visits will take place every 6 months. An overview of data capture can be found listed in Table 1.

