## Figures and Tables

**Figure 1 fig1:**
[figure not shown]
Flow diagram of enrollment, intervention, and assessments.

**Table 1 tab1:** Schedule of enrollment, allocation, visits, and assessments.

Time of visits	Enrolment	Allocation	Drug intervention period				Follow-up period			
	−2w	0w	4w, 8w	12w	16w, 20w	24w	12 m	18 m	24 m	30 m
*Collect basic medical history*										
Sign informed consent form	√									
Determine inclusion and exclusion criteria	√	√								
Determine withdrawal criteria	√	√	√	√	√	√	√	√	√	√
Fill in general information	√	√								
History of prediabetes and treatment	√									
Comorbidity and symptom	√									
Physical examination and consultation	√	√	√	√	√	√	√	√	√	√
Concomitant medication	√	√	√	√	√	√	√	√	√	√

*Efficacy assessment*										
Glycosylated hemoglobin		√		√		√	√	√	√	√
Fasting plasma glucose		√	√	√	√	√	√	√	√	√
2-hour postprandial blood glucose		√	√	√	√	√	√	√	√	√
Blood lipids		√		√		√	√	√	√	√
Carotic artery intima-media thickness		√		√		√	√	√	√	√
BMI, waist perimeter and hip perimeter, waist-hip ratio, and blood pressure		√	√	√	√	√	√	√	√	√
TCM symptom score		√		√		√	√	√	√	√

*Safety assessment*										
Vital signs		√				√	√	√	√	√
Routine blood, urine, and stool examination		√				√	√	√	√	√
Liver function		√				√	√	√	√	√
Renal function		√				√	√	√	√	√
Electrocardiogram		√				√	√	√	√	√
Hypoglycemic episodes			√	√	√	√	√	√	√	√
Adverse events			√	√	√	√	√	√	√	√

*Other work*										
Record of TCPMs		√	√	√	√	√	√	√	√	√
Research summary						√				√

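### Glucose is read at six on-treatment visits, but section 2.11 names only unadjusted two-sample tests with LOCF, so unless visits are averaged first the primary changes are analysed less precisely than the data allow

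*Protocol article*

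**What the plan says.** Section 2.6.2 (Primary Outcome): "The primary outcome is the changes of fasting plasma glucose (FBG), two-hour postprandial blood glucose (2h PBG), and glycosylated hemoglobin (HbA1c"). It then sets the frequency: "Blood glucose is evaluated every 4 weeks, and HbA1c is evaluated every 12 weeks". No visit or summary of visits is named for the change.

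Section 2.7: "The study is divided into two periods, a 24-week drug intervention period and a 24-month follow-up period". Table 1 ticks the row "Fasting plasma glucose" and the 2-hour glucose row at weeks 0, 4, 8, 12, 16, 20 and 24, then at 12, 18, 24 and 30 months. HbA1c is ticked at weeks 0, 12 and 24 and at the same four follow-up visits.

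Section 2.11, on measurement data: "compared between groups using the group *t*-test, Fisher's exact test, or Wilcoxon rank sum test". On missing values: "The last observation carried forward (LOCF) method will be used for the missing data supplement". On the error level: "All statistical tests are two-sided tests, and *P* < 0.05 will be considered statistically significant". No repeated-measures model, within-person summary or baseline covariate appears.

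**The concern.** Each two-sample test takes one number per person. A change from baseline to one visit uses two of the seven glucose readings in the treatment period. The alternative reading, one test per visit, uses the readings separately and never combines them. Neither version adjusts for the baseline value. Missing visits are filled with LOCF values, although the Discussion itself expects the long treatment and follow-up to cause poor compliance.

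This matters because the sample size in section 2.10 is built on conversion to diabetes, and no power calculation in the article covers the glucose or HbA1c changes. Wider intervals than necessary on declared primary outcomes make a real difference easier to miss, and the readings that could narrow them are already scheduled in 600 people.

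**Working it through.** The plan gives no precision or power figure for these outcomes, so there is none to reproduce.

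**Inputs from the article:** baseline plus six on-treatment glucose readings (section 2.6.2, Table 1), and two-sided 0.05 tests (section 2.11).

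**Assumptions:** equal variance at every visit, in units of σ², and arms with similar baseline means. Three correlation patterns are used:
- equal correlation ρ between all visits, 0.4 to 0.8;
- mild decay, ρ falling by 5-10% per 4 weeks;
- AR(1), with adjacent-visit correlation 0.5 to 0.9.

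**1. Baseline adjustment at week 24.** Let r be the correlation between baseline and week 24. The unadjusted change has variance 2(1−r); the baseline-adjusted value has 1−r². The ratio is (1+r)/2.
- Equal correlation 0.8: √0.90 = 0.949, interval 5% narrower. At 0.4: √0.70 = 0.837, 16% narrower.
- Mild decay: 11% (r = 0.8×0.95⁶ = 0.588) to 22% (r = 0.4×0.90⁶ = 0.213) narrower.
- AR(1) at 0.5: r = 0.5⁶ = 0.016, √0.508 = 0.713, 29% narrower.

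**2. Earlier visits and the week-24 contrast.** With complete data and a separate mean for each visit, a repeated-measures model gives a variance ratio of 1.00 to the simple week-24 change: no gain. With 10% to 20% monotone dropout, the ratio to complete cases is about 0.96 to 0.89.

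**3. Average of weeks 16, 20 and 24, no baseline adjustment.** Under equal correlation, the mean of k readings minus baseline has variance ((k+1)/k)(1−ρ), so the ratio to a single-visit change is (k+1)/(2k), whatever ρ is. For k = 3 it is 4/6 = 0.667; √0.667 = 0.816, 18% narrower. Mild decay gives 14-17%. AR(1) gives 11-12% (for example, ratio 0.795 at 0.7).

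**4. Power.** Take an effect with 80% power on a single-visit change: 1.96 + 0.842 = 2.802 standard errors.
- Constant effect over the three visits, equal correlation: Φ(2.802/0.816 − 1.96) = 93%. AR(1) at 0.7: Φ(2.802/0.892 − 1.96) = 88%.
- Effect growing linearly to week 24: the three-visit mean carries (4/6 + 5/6 + 6/6)/3 = 5/6 of the week-24 effect. Equal correlation: Φ(2.802×0.833/0.816 − 1.96) = 82%. AR(1) at 0.7: Φ(2.802×0.833/0.892 − 1.96) = about 75%, a small loss.

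**The case against.** A reader might infer that the plan discards the repeated readings. The article does not say so. It never states which value enters the test, and a *t*-test on each person's mean on-treatment change would fit section 2.11 as written and keep the precision of averaging. This stands, and it is why the point is conditional.

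A second tempting reading is that using all six visits is worth far more. Under equal correlation the six-visit mean has a ratio of 7/12 = 0.583: 42% less variance, a 24% narrower interval, the equivalent of 71% more participants, and 96% power in place of 80%. Those figures hold only for a six-visit average with a constant effect, a different question from change at week 24. If the effect grows linearly, that average carries 7/12 of the week-24 effect and power falls to about 57%. Slow growth is plausible, since section 2.5.1 sets its weight-loss goal over 6-8 months. One model yields both contrasts, but the precision of the average does not pass to the week-24 contrast.

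Third, the six readings apply to glucose only. HbA1c has two on-treatment values.

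Finally, the article is condensed, and visit definitions and model details often sit in an analysis plan. But section 2.11 does not leave the method open: it names the tests and the imputation rule, and those named choices can be compared with the visit schedule.

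**Conclusion.** The point holds in conditional form. The named analysis is unadjusted, works on one value per person, fills gaps with LOCF, and states no averaging of visits. Unless visits are averaged first, the primary changes are estimated less precisely than the scheduled data allow.

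The most dependable gain is from baseline adjustment at week 24: about 5-16% under equal correlation of 0.8 to 0.4, and up to about 29% if correlation decays quickly. The weeks 16-24 average is 11-18% narrower, but its power advantage (88-93% against 80%) needs a roughly constant effect over those visits. With linear growth it is about 82% under equal correlation and can fall below 80% under faster decay. Earlier visits help the week-24 contrast only when data are missing.

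All of this rests on assumed correlations. It concerns precision only. Participants choose their own group, and a better model of the repeated readings does not remove that confounding. If the arms differ at baseline, the adjusted difference and the difference in change are also not the same quantity.

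**What to change.** In section 2.11, replace the two-sample tests for the three primary outcomes with one mixed model for repeated measures per outcome: arm, visit, arm-by-visit, baseline value and unstructured within-person covariance, fitted to observed readings in place of LOCF values. Name the week-24 contrast as the main on-treatment result. Report the weeks 16-24 average for fasting and 2-hour glucose alongside it, and weeks 12 and 24 for HbA1c. Report the four follow-up visits as separate contrasts so that the treatment and follow-up periods are not mixed. If a per-person average is what the sponsor already intends, state which visits it covers; that would answer the averaging part of the point, but not baseline adjustment or LOCF.

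The cost is analysis wording and slightly more analysis work, with no new visits, data or participants. The average understates an effect still growing at week 24, which is why the week-24 contrast stays the main result.
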